## Abstract

**Background:**

Chronic neck pain is a common complaint in the Netherlands with a point prevalence of 14.3%. Patients with chronic neck pain are often referred to a physiotherapist and, although many treatments are available, it remains unclear which type of treatment is to be preferred.

The objective of this article is to present the design of a randomised clinical trial, Ephysion, which examines the clinical and cost effectiveness of behavioural graded activity compared with a physiotherapy treatment for patients with chronic non-specific neck pain.

**Methods:**

Eligible patients with non-specific neck pain persisting longer than 3 months will be randomly allocated to either the behavioural graded activity programme or to the physiotherapy treatment. The graded activity programme is based on an operant approach, which uses a time-contingent method to increase the patient's activity level. This treatment is compared with physiotherapy treatment using a pain-contingent method.

Primary treatment outcome is the patient's global perceived effect concerning recovery from the complaint. Global perceived effect on daily functioning is also explored as primary outcome to establish the impact of treatment on daily activity. Direct and indirect costs will also be assessed. Secondary outcomes include the patient's main complaints, pain intensity, medical consumption, functional status, quality of life, and psychological variables. Recruitment of patients will take place up to the end of the year 2004 and follow-up measurement will continue until end 2005.

## Background

### Prevalence and incidence

Neck pain is a common complaint that causes substantial morbidity in western countries with a reported prevalence ranging from 9.5 to 22% [1,2]. Of all musculoskeletal pains in the Netherlands, neck pain is one of the three most reported with a point prevalence of 21%; it is more often reported by women than men [3]. In 1996 total related costs were estimated to be US $686.2 million, which is about 1% of the total Dutch health care expenditures [4]. Most neck complaints are continuous or recurrent [3]. When the neck pain persists for more than 3 months it is defined as chronic, and the related prevalence is 14.3% [3,5]. Although the prevalence of neck pain is stable over different age groups, the incidence of chronic neck pain increases with age [3,6].

There are many potential causes of neck pain, but mostly no specific underlying pathology is found so that it is designated as non-specific [7]. Although not a life- threatening disease, neck pain can negatively affect patients' quality of life, cause pain and stiffness, and may result in substantial medical consumption, absenteeism and disability [4,8].

In the Netherlands, patients with neck pain are often referred for physiotherapy. Moreover, physiotherapy accounted for 84% of the total direct medical neck pain costs in 1996 [4]. Although physiotherapists can apply various treatments, no formal guidelines are yet available.

### Treatment models

Two treatment models have been described in the literature, both of which are applicable within the field of physiotherapy. The first, a biomedical model, considers pain to be a sign of physiological damages and treatment according to this model aims to remove the pathologic condition so that the pain will no longer occur [9,10]. Moreover, treatment is guided by the amount of pain a patient experiences, leading to a pain-contingent approach [11]. According to the second, a biopsychosocial model, pain is not necessarily caused by underlying pathology or impairment but can persist long after the initial pathology has healed; psychological and social factors may be important in the development and maintenance of complaints [12,13]. According to the principles of this biopsychosocial model, behavioural therapies assume that maladaptive behaviours are learned and, therefore, can be modified through new learning experiences [10,14]. Three different approaches are known: respondent, operant and, cognitive behavioural therapy [9,15,16]. The present study mainly employs an operant behavioural approach, as described by Fordyce and applied by Lindström et al [11,17]. According to this approach, the treatment focuses on decreasing pain behaviour (operants) and increasing healthy behaviour, and consists of behavioural graded activity on a time-contingent basis [11,18].

### Available evidence

Many conservative physiotherapeutic treatments are available for treating neck pain, but there is insufficient evidence to allow to conclude that one type of treatment is more effective then others [19,20].

In a review on chronic pain, operant behavioural therapy was found to be beneficial to waiting list control groups on outcomes such as pain experience, mood effect other than depression, social role, and for the expression of pain behaviour [21]. Compared to other treatments, operant behavioural therapy is only beneficial for the expression of pain behaviour and role functioning [21]. Another review showed little evidence that biopsychosocial multidisciplinary rehabilitation is more effective than other rehabilitation methods for neck and shoulder pain, but the authors found only two relevant studies that satisfied the criteria for their review [22]. When examining the effectiveness of behavioural treatment for chronic pain another difficulty is that no standard protocol exists for the application of these treatments. As a result, a wide range of techniques described in the literature has been labelled as behavioural [23].

In summary, it remains unclear which type of conservative, including behavioural, treatment is to be preferred in the management of chronic neck pain. Therefore, this study, Ephysion (Effectiveness physiotherapy in neck pain), aims to evaluate the clinical and cost effectiveness of an operant behavioural programme (i.e. behavioural graded activity) compared with a physiotherapy treatment in patients with chronic non-specific neck pain. In addition, we aim to identify subgroups of patients who benefit most from one of the two treatments, and to identify the most important determinants for recovery from chronic non-specific neck pain.

### Why a design article

Because a biased study design can produce incorrect conclusions, the design of a trial should be carefully examined before adopting its conclusions [24]. A design article allows to examine the design objectively without being influenced by the study results, to check any resulting articles for protocol deviations, and may also reduce the temptation to search for associations during data analysis rather then presenting hypotheses in advance [25]. Further, a published protocol informs others about which studies are in process thus reducing duplication of research effort [25]. Finally, a design article prevents publication bias in the case that future articles are not published, because study results can be retrieved from the author and the study can therefore still be included in future reviews [25,26].

## Methods

### Study design

A randomised clinical trial (RCT) has been designed to assess the effectiveness of behavioural graded activity compared with physiotherapy treatment in patients with chronic non-specific neck pain. The study design has been approved by the Medical Ethics Technical Commission of the Erasmus MC, University Medical Centre in Rotterdam and is in compliance with the Helsinki Declaration.

### Selection of patients and informed consent

Forty general practitioners (GP) in region West Brabant in the Netherlands will select the patients. Patients are eligible if they are aged between 18 and 70 years old, have suffered from neck pain for over three months, and have an adequate knowledge of the Dutch language. Excluded are patients diagnosed with a specific disorder (e.g. a slipped disc, a tumour or a lesion in the cervical spine), those who have had physical/manual therapy during the previous six months, those with a chronic disease (e.g. rheumatoid arthritis or coronary artery disease), or those who have to undergo surgery in the near future. Eligible patients will receive an information leaflet from their GP and the GP then informs the research department.

Thereafter, the research assistant contacts the patient, provides additional information about the implications of participation, re-checks the eligibility of the patient, and completes the informed consent procedure.

### Sample size

The sample size for this study is calculated according to the global perceived effect (GPE). Based on previous studies, a 20% difference in GPE is expected after completion of either treatment (9 weeks) and is considered to be clinically relevant; 160 patients are needed to detect this difference. In this calculation a power (1 - β) of 80% is taken into account. Thus, the inclusion of 80 patients per treatment group is planned.

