### Physiotherapists and Interventions

After receiving written information, 34 physiotherapists in region West Brabant will participate in either the physiotherapy treatment (PT) or the graded activity programme (GAP). To optimise the contrast between the two treatments, both groups are strictly separated throughout the study. The PT group consists of 16 physiotherapists and the GAP group of 18 physiotherapists. The PT physiotherapists participate in a meeting to standardize the physiotherapy treatment. The GAP physiotherapists are instructed on the behavioural graded activity approach during a two-day theoretical and practical training course.

Both interventions are performed in an outpatient setting. A maximum of 18 treatments per patient is set and each treatment takes about 30 minutes, which is in accordance with medical insurance policy in the Netherlands. Before treatment starts, physiotherapists receive a completed questionnaire about the patient's main complaints [29]; this questionnaire reveals the three daily activities which are considered the most important complaints to the patient. Physiotherapists can use these three activities in the process of formulating the patient's primary therapy aim. In both treatments, the physiotherapist starts with a physical examination of the patient and an anamnesis. Then an individually tailored program will be applied and the process recorded after each treatment session using a specially designed form.

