### Analyses

Descriptive statistics will be used to examine comparability of baseline data between PT and GAP, and to check if randomisation was successful. Before this analysis, decisions about differences considered to be clinically relevant are made and, if necessary, adjustment will be made for these differences in multivariate analysis. Further, all outcome data will be screened for normality and, if necessary, logarithmic transformations or non-parametric methods of analysis will be applied.

The first aim is to evaluate the clinical and cost effectiveness of GAP compared to PT. Clinical effectiveness will be examined with a Student's t-test (continuous), a Chi-square test (dichotomised) or a Wilcoxon test (not normally distributed) according to the intention-to-treat principle. This means that patients will be analysed in the treatment group to which they are randomly allocated. For missing data, imputation techniques will be used. When the dropout rate is 10% or more, or loss to follow-up is 20% or more, per-protocol analysis will be performed. The results on primary outcome will be dichotomised into improved versus not improved. Improved implies completely recovered and much improved, whereas not recovered implies slightly improved, not changed, slightly worsened, much worsened, and worse than ever [31].

Cost effectiveness will be calculated from a societal perspective. Costs (direct as well as indirect) will be related to the treatment effects, based on the primary outcome measure, by calculating cost-effectiveness ratios.

The second aim is to identify subgroups of patients that benefit most from one of the two treatments. The following subgroups will be investigated: duration and severity of the complaint, depression, and fear of movement.

The third aim is to identify important variables for recovery. For this purpose multivariate analysis will be performed to investigate the influence of prognostic variables and patient characteristics on the outcome. Separate analyses will be conducted to investigate prognostic factors for short-term (3 months) and long-term (12 months) recovery.

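### The number needed for 80% power equals the number to be included, so the stated power holds only with complete outcome data and independent patients

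*Protocol article*

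**What the plan says.** The Sample size section of the protocol article bases the calculation on global perceived effect. It states that "a 20% difference in GPE is expected after completion of either treatment (9 weeks"), that the power is 80%, and that "160 patients are needed to detect this difference". The next step is "Thus, the inclusion of 80 patients per treatment group is planned". Two groups of 80 make 160, so the inclusion target is the required number with nothing added.

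Other sections bear on whether 160 patients will yield 160 independent outcomes:

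- Analyses: "The results on primary outcome will be dichotomised into improved versus not improved", and dichotomised outcomes are compared with a Chi-square test. Missing values are to be imputed. The section adds: "When the dropout rate is 10% or more, or loss to follow-up is 20% or more, per-protocol analysis will be performed".
- Outcome measurement: every outcome comes from a mailed questionnaire.
- Physiotherapists and Interventions: "The PT group consists of 16 physiotherapists and the GAP group of 18 physiotherapists". The two groups are kept apart, so each therapist treats in one arm only.
- Randomisation: patients choose a therapist within their arm once they have been allocated.

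**The concern.** If 160 is the number required, it is the number that must be analysed, and the patients must carry independent information. The plan includes that number and no more, while other sections foresee missing outcomes and a structure in which patients share therapists. Either feature reduces the effective sample size below 160, and hence the power below the stated 80%.

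This is the only justification of the sample size in the article. A non-significant result would be read against the 80% figure, and readers would rule out a 20-point difference with more confidence than the design gives.

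**Working it through.** **Inputs from the article.** Difference 20%, power 80%, 80 per arm, binary outcome, Chi-square test (Sample size; Analyses). Therapists: 16 + 18 = 34 (Physiotherapists and Interventions).

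**Assumptions of mine.** Two-sided 5% test; the 20% is an absolute difference; a range of improvement rates; loss of 0, 10 or 20% with no information recovered by imputation; therapist ICC of 0 or 0.05.

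**Formulas.** With rates p1 and p2, mean p̄, difference d and n per arm (pooled variance under the null, no continuity correction):

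- n = {[1.96·√(2p̄(1−p̄)) + 0.8416·√(p1(1−p1)+p2(1−p2))] / d}²
- power = Φ{[d·√n − 1.96·√(2p̄(1−p̄))] / √(p1(1−p1)+p2(1−p2))}

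**Step 1: reproduce 160.** At 19% against 39%, p̄ = 0.29, √(2 × 0.29 × 0.71) = 0.6417 and √(0.1539 + 0.2379) = 0.6259. Then n = [(1.2578 + 0.5268)/0.20]² = 79.6, so 80 per arm and 160 in total. The mirror pair, 61% against 81%, gives the same. The stated figure is therefore attainable with ordinary inputs.

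**Step 2: remove patients or independence from that case.**

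- Complete data, n = 80: (1.7889 − 1.2578)/0.6259 = 0.849, power 80.2%.
- 10% loss, n = 72: (1.6971 − 1.2578)/0.6259 = 0.702, power 75.9%.
- 20% loss, n = 64: (1.6000 − 1.2578)/0.6259 = 0.547, power 70.8%.
- ICC 0.05 without loss: an average of 80/17 = 4.7 patients per therapist gives a design effect of 1 + 3.7 × 0.05 = 1.185 and an effective n of 80/1.185 = 67.5. Then (1.6432 − 1.2578)/0.6259 = 0.616, power 73.1%. Even caseloads are assumed; uneven ones would raise the design effect.

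**Step 3: does this depend on 19% against 39%?** Not if the word needed is taken literally. When 80 per arm gives exactly 80% power and a fraction r of the information remains, power is approximately Φ[(1.96 + 0.8416)·√r − 1.96]. This is 75.7% at r = 0.9, 70.7% at r = 0.8 and 73.0% at r = 67.5/80. With a one-sided 5% test, 1.645 replaces 1.96 and the results are 76.2%, 71.9% and 73.9%.

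**Step 4: other improvement rates, two-sided 5%.**

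| Rates | n needed per arm | Power, 80 per arm | 10% loss | 20% loss | ICC 0.05, no loss |
|---|---|---|---|---|---|
| 10/30 or 70/90 | 62 | 89.3% | 85.9% | 81.5% | 83.5% |
| 19/39 or 61/81 | 80 | 80.2% | 75.9% | 70.8% | 73.1% |
| 20/40 or 60/80 | 82 | 79.4% | 75.0% | 69.9% | 72.2% |
| 30/50 or 50/70 | 93 | 73.7% | 69.1% | 63.9% | 66.3% |
| 40/60 | 97 | 72.0% | 67.3% | 62.1% | 64.5% |

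At 10/30 or 70/90, 20% loss together with an ICC of 0.05 gives 76.2%.

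**Step 5: difference detectable with 80% power** from an assumed PT (physiotherapy arm) rate of 40%, independent patients: 22 points with 80 per arm, 23 points with 72, and 24.5 points with 64.

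**The case against.** The strongest reply is that the figure is not shown to be wrong. It reproduces at rates that are not extreme for an outcome defined as completely recovered or much improved. Alpha, sidedness, rates, expected loss and ICC are details that a condensed article may leave to the full protocol, and their absence is not held against it here. The full calculation might already contain an allowance for loss. With a one-sided 5% test, 80 per arm gives at least 81.7% at every rate with complete data.

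The 10% and 20% figures in the Analyses section trigger a per-protocol analysis and forecast nothing. The trial is sized on the 9-week outcome, where loss may be lower than at 52 weeks. Imputation is also planned, so removing a full 10% or 20% of the information is an assumption.

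Much of this stands, and it rules out stronger readings that a reader might infer: that 160 can be obtained only from a one-sided test or a particular variance formula, that it needs an extreme improvement rate, or that the trial's real power is 60–75%. The last would need a known alpha, rate, loss and ICC, and the article gives none of them.

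The wording of the Sample size section remains: it calls 160 the number needed to detect the difference and derives the inclusion target directly from it. A hidden allowance would contradict that. It would also require a two-sided 5% test to have 80% power with 72 per arm (lower-arm rate of about 14% or less, or 66% or more) or with 64 per arm (about 11% or less, or 69% or more). Imputation limits bias and may recover some information, but it does not in general restore all that was lost.

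**Conclusion.** The concern holds in a limited form. As written, the 80% applies to 160 patients with complete outcomes and no correlation within therapist, and the article's own provisions make both conditions doubtful. Taking the stated number at its word, the shortfall is about 4 points of power with 10% loss, 9 points with 20% loss and 7 points with an ICC of 0.05 alone. Those loss rates and that ICC are illustrative.

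The absolute level of power cannot be fixed from the article. Under a two-sided 5% test without clustering and with 0–20% loss, it runs from 62% (40% against 60%, 20% loss) to 89% (10% against 30%, or 70% against 90%, no loss). Moderate importance: the design is not invalid, but the power figure is more favourable than the described conditions support.

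**What to change.** Keep 160 patients. In the Sample size section, say that 80% power applies to 160 analysable, independent patients. Then add one of the following, with its assumptions beside it:

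- the power that remains after a stated assumed loss at 9 weeks and a stated therapist design effect; or
- the difference detectable with 80% power, which from an assumed PT rate of 40% is about 22 points with complete data and about 25 points with 20% loss (independent patients, two-sided 5%).

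The cost is a few sentences and no extra patients or visits. The downside is that the stated power becomes somewhat less favourable.

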### Randomisation

An independent examiner using a computer-generated randomisation schema performs randomisation. To prevent unequal distribution, patients are pre-stratified based on three important prognostic factors: gender, age and the severity of the complaint, which are recorded at baseline [27]. Further, unequal group sizes are prevented by using a 6-block randomisation that equalizes allocation to the two treatment groups per stratum after every sixth patient [28]. After randomisation, patients choose a physiotherapist within the allocated treatment group. Then, to ensure that the treatment starts as soon as possible, the research assistant makes the first appointment for treatment.

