### Blinding

Patients are told to receive physiotherapy but are blinded to allocation of the two treatments; the content of the treatments is not described in the information leaflet. This enhances the quality of the study, because the patients themselves measure the effect of treatment. GPs are also blinded for allocation to prevent accidentally informing the patients of the allocated treatment. The physiotherapists are not blinded for allocation, but the physiotherapists from each treatment group are kept strictly separate and are not involved in the outcome measurement. Finally, the primary investigator is blinded for patients' allocation but the research assistant is not; neither is involved in the outcome measurement.

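### Fixed blocks of six per stratum, with an unblinded research assistant who both enrols patients and books them into the allocated arm, leave later allocations partly guessable at enrolment

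*Protocol article*

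**What the plan says.** All references are to the protocol article.

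- **List and release** (Randomisation): "An independent examiner using a computer-generated randomisation schema performs randomisation".
- **Stratification** (Randomisation): "patients are pre-stratified based on three important prognostic factors: gender, age and the severity of the complaint". The number of levels for age and severity is not given.
- **Blocks** (Randomisation): "unequal group sizes are prevented by using a 6-block randomisation that equalizes allocation to the two treatment groups per stratum after every sixth patient". This is one constant size, stated in the article itself, which describes recruitment as continuing to the end of 2004.
- **Before allocation** (Selection of patients and informed consent): after referral by the GP, the research assistant contacts the patient, gives further information, "re-checks the eligibility of the patient, and completes the informed consent procedure".
- **After allocation** (Randomisation): the patient chooses a therapist from the allocated group, and then "the research assistant makes the first appointment for treatment".
- **Blinding**: "the primary investigator is blinded for patients' allocation but the research assistant is not". GPs are blinded, and the assistant takes no part in measuring outcomes.
- **Timing** (Outcome measurement): baseline questionnaires go out after inclusion.

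**The concern.** One role sits on both sides of the allocation step. Therapists of the two arms are kept strictly separate, so booking an appointment reveals the arm. The same person then informs, re-checks and consents the next patient. With a constant block of six, every allocation already seen in a stratum changes the odds for those remaining, and late in a block it can settle them.

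The independent examiner protects the list from being read, but does not prevent inference from assignments already made. A person with a view of the likely next arm could, even unintentionally, press harder or less hard for consent, read a borderline criterion differently, or delay a contact. The arms would then differ in who enters them. Blinded patients and mailed questionnaires guard against biased reporting of outcomes, not against this, and analysis cannot reliably repair it.

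**Working it through.** **Inputs.** Block of six, 3:3, within strata (Randomisation); 160 patients (Sample size). The article reports no predictability figure, so there is none to reproduce. Assumed: 8, 12 or 18 equally likely strata, as a range and not a reconstruction, and an observer who knows the block size and all past allocations by stratum. The observer guesses the likelier arm; a tie counts one half.

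**Step 1: one complete block, stratum known.** There are C(6,3) = 20 possible sequences.

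An allocation is certain once one arm has used its three places:
- 4th place: the first three are all the same arm, 2/20 = 0.10.
- 5th place: the last two are the same arm, 2 × 4/20 = 0.40.
- 6th place: always, 1.00.
- Sum: 0.10 + 0.40 + 1.00 = 1.5 of 6, or 25%.

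Probability that the best guess is right:
- 1st: 0.50.
- 2nd: 3/5 = 0.60.
- 3rd: 0.4 × 3/4 + 0.6 × 1/2 = 0.60.
- 4th: 0.1 × 1 + 0.9 × 2/3 = 0.70.
- 5th: 0.4 × 1 + 0.6 × 1/2 = 0.70.
- 6th: 1.00.
- Sum: 4.1 of 6, or 68.3%, against 50% under full concealment.

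**Step 2: 160 patients with unfinished blocks.** The average stratum holds 160/8 = 20, 160/12 = 13.3 or 160/18 = 8.9 patients, that is about 3.3, 2.2 or 1.5 blocks. Certain allocations fall at the end of blocks, so unfinished blocks lose them. This was simulated (2,000 repetitions).

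**Step 3: severity unknown at consent.** Severity is recorded at baseline and the questionnaire follows inclusion, so the assistant may know only gender and age at consent. With two severity levels assumed, the next patient belongs to one of two strata. The allocation is certain only if both have exhausted the same arm. This was simulated (4,000 repetitions).

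**Step 4: hidden block sizes of 4, 6 and 8 in random order.** The stratum is known, and the observer knows the set of sizes but not which one is in use (2,000 repetitions).

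| Strata assumed | Fixed 6, stratum known: certain | Best guess | Fixed 6, severity unknown: certain | Best guess | Hidden 4/6/8, stratum known: certain | Best guess |
|---|---|---|---|---|---|---|
| 8 | 35.9 (22.4%) | 67.1% | 4.4 (2.7%) | 63.4% | 3.8 (2.4%) | 66.9% |
| 12 | 33.8 (21.1%) | 66.5% | 4.1 (2.6%) | 63.0% | 3.9 (2.4%) | 66.3% |
| 18 | 30.6 (19.1%) | 65.6% | 3.7 (2.3%) | 62.3% | 3.5 (2.2%) | 65.5% |

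Certain allocations are counted out of 160.

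**Step 5: the enrolling person sees no past allocations.** Nothing can be inferred: none are certain, and guessing accuracy is 50%.

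Varying the block size thus removes nearly all certain predictions but moves the best guess by 0.1 to 0.2 percentage points. Separating the roles removes both.

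**The case against.** Permuted blocks of fixed size, held by an independent examiner with a computer-generated list, are a recognised design. The article is a condensed account, and whether the assistant had the block size or a log of strata during enrolment may be settled in the full protocol. Blinded GPs make the first selection. Most criteria that the assistant re-checks are factual, such as age, duration of pain, recent therapy and planned surgery. The assistant neither treats nor measures outcomes, and no preference for an arm is documented. Exploiting the blocks would need a running tally across several strata.

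Most of this stands and limits the strength of the point. It does not remove it, because the dual role and the constant block are stated outright, and encouragement at consent is not a factual criterion.

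A reader might infer three stronger things that the document does not support:
- **A quarter of the trial, 0.25 × 160 = 40 patients, is predictable.** That needs every block to be complete and every stratum to be known at consent. Stratification by three factors leaves unfinished blocks, and the timing of the questionnaire makes it doubtful that severity is known. In that case the certain cases fall roughly tenfold, to about 4.
- **Concealment was broken or allocation manipulated.** Nothing in the text shows this. The list itself is protected.
- **Recording eligibility, consent and baseline data as final before allocation would cure it.** That largely repeats the order already described, and does not stop a guess made before consent is complete.

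**Conclusion.** The point holds as a risk at enrolment. It comes from combining the Randomisation, Selection and Blinding sections, and the block size alone would not establish it. The size depends on what the assistant knows when seeking consent:

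- Stratum known: about 31 to 36 of 160 allocations certain (19–22%), best guess right about 66–67% of the time.
- Severity not yet known, which the order of events suggests: about 4 of 160 certain, best guess still right 62–64% of the time.

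Both assume that the assistant knows the block size and tracks strata, which the article neither states nor rules out. They also assume 8 to 18 equally filled strata and, in the second case, two severity levels. Under these assumptions prediction stays above chance in every case examined. The resulting bias in the treatment effect cannot be derived from the document. The change is worth making while recruitment continues, but the point does not invalidate the trial.

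**What to change.** For patients not yet randomised:

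1. **Separate the roles.** Give the booking of the first appointment, together with the patient's choice of therapist, to an existing role outside eligibility and consent, for example the independent examiner or the chosen physiotherapy practice. Keep past allocations from the enrolling assistant and amend the Blinding section to say so. This step returns guessing to 50%.
2. **Vary the blocks.** Have the independent examiner regenerate the remaining list with randomly varying, undisclosed block sizes, for example 4, 6 and 8. This cuts certain predictions to about 4 of 160 or fewer if an allocation becomes known despite step 1. It hardly changes guessing accuracy and should not stand alone.

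Cost: a new list for the remaining patients, a short procedural text and a small shift of administrative work. Chance imbalance within a stratum can be slightly larger, since a block of eight can be up to 4 patients out of balance partway through, against 3 for a block of six.
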